#### Quantitative data

Quantitative data will be collected through a number of sources, including: checklists, completion of program sessions and survey answers. Descriptive statistics of process measures will be summarised [10]. A correlation matrix (ranked) will determine any relationships between the process measures.

*Program adherence (fidelity)* will be measured through the score attained in the fidelity tool checklist as well as the variability in score attained in the domains within the fidelity checklist (Additional file 1: Appendix 1). For the initial session, there are 39 program delivery components the O&M Specialist will be scored on, on a scale of 1 to 3, where 1 = not done, 2 = could improve, 3 = well delivered (range 39 to 117). These components are separated into the domains: introduction, v-LiFE assessment tool, key points of the program explained, balance principles, strength principles, teaching the activity, planning and recording, and wrap up. For sessions two to six, there are 29 program delivery components the O&M Specialist will be scored on (range 29 to 87), using the same three point scoring method above. These components are separated into the domains: review of activities since last visit, teaching the activities, v-LiFE principles of balance and strength training reinforced, key points of program reinforced, safety reinforces, planning and recording, and wrap up at the end of the session.

*Complete delivery (dose delivered)* will be measured through number of v-LiFE sessions and phone calls delivered to participants by O&M Specialists, as a continuous variable (range 0 to 11). Program session data will be extrapolated from Guide Dogs CRM database.

*Participant receipt (dose received)* will be measured using AFRIS. This will be measured as a continuous variable (range 6 to 42) where higher scores indicate greater engagement in v-LiFE [15].

*Participant enactment* will be measured using the Self-Report Habit Index as a continuous variable (range 12 to 60). A score of 36 or higher indicates the presence of a habit. Lower scores indicate the absence of a habit [17].

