#### The training component

More than 50 O&M Specialists from 10 offices, in six regions of NSW/ACT, will participate in two days of training. To assist in training and participation of those in regional areas, O&M Specialists will be able to take part in one of three possible training sessions (two will take place in Sydney NSW, and one in Northern NSW). The first day of training will consist of training in the delivery of the v-LiFE program and the second day will consist of training in research procedures. Each session will be facilitated by the same trainers (v-LiFE program: LC, JM).

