#### Program adherence

Program adherence (fidelity) is a measure of what extent the intervention was developed and used as intended [11]. The theoretical underpinning of v-LiFE is habit retraining [14]. As there are more than 50 O&M Specialists delivering the program, it is important to assess whether all the participants are receiving equivalent training. O&M Specialists need to encourage the participants to incorporate the skills they learn through sessions into everyday activities. This self-efficacy is facilitated through: positive reinforcement from the instructor, self-monitoring and setting achievable short-term goals.

Program adherence will be measured through direct observation of participant sessions by an observer trained in the delivery of v-LiFE. Each instructor will be observed completing 1–2 sessions with participants, to cover approximately 20% of all v-LiFE program participants. A v-LiFE fidelity tool checklist (Additional file 1: Appendix 1) will be used in each observation to ensure consistency in assessment. The checklist is designed to assess whether sessions adhere to the program as designed and set out in the program manual, and the quality of delivery, including: content, key features, credibility, skill, language, verbal and active teaching strategies. Wherever possible, the observer will also provide feedback to the Instructor to improve service delivery.

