#### Sample size

The PlaTFORM study was powered to be able to compare fall rates between control and intervention arms of the main RCT and required a total of 588 participants (294 per group) to detect a 30% between-group difference in falls rate, with 90% power at the 5% level, allowing for a 15% drop-out [9]. Consequently, quantitative data from up to 294 participants will be available for the process evaluation. This sample size will be sufficient to quantify the variation in scores for program fidelity, dose delivered, dose received through the AFRIS scale and enactment through the habit formation index. For qualitative data, it is expected this sample size will enable thematic saturation.

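### The ranked correlation matrix mixes a specialist-level fidelity score with participant-level scores and does not use the nesting of participants in specialists

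*Protocol article*

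**What the plan says.** The Quantitative data section of the protocol article promises descriptive statistics of the process measures and then one analysis of how they relate: "A correlation matrix (ranked) will determine any relationships between the process measures".

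The measures entering that matrix sit at two levels.

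- Fidelity is a score of the specialist's delivery. For the initial session, "there are 39 program delivery components the O&M Specialist will be scored on". Under Program adherence, "Each instructor will be observed completing 1–2 sessions with participants, to cover approximately 20% of all v-LiFE program participants".
- Dose delivered, AFRIS and the habit index are recorded for each participant (Quantitative data).

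The nesting is described in the same article. The training component refers to "More than 50 O&M Specialists from 10 offices, in six regions of NSW/ACT", and the Sample size section says that "quantitative data from up to 294 participants will be available for the process evaluation". That section judges this sample sufficient to describe variation in all four measures, fidelity included.

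The article also expects specialists to differ: "As there are more than 50 O&M Specialists delivering the program, it is important to assess whether all the participants are receiving equivalent training". Strengths and limitations returns to possible inconsistency between specialists.

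**The concern.** A plain rank correlation treats each row as a separate, independent unit. Here the participants of one specialist share that specialist's skill, style and office, so their dose, receipt and habit scores may resemble each other. A fidelity score belongs to the specialist. If it is attached to everyone that specialist treated, one observation appears several times.

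The article does not say which pairs form the fidelity row. It could rest on about 50 specialists, about 59 observed participants or up to 294 participants, and these carry very different amounts of information. The row matters because the overarching aim in Methods is to relate implementation to outcomes. The Discussion also expects the evaluation to help separate the effect of implementation from that of the program itself. A link between fidelity and habit that was read with the confidence of 294 independent pairs could mislead on that question.

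**Working it through.** **Inputs from the article.** Up to 294 intervention participants (Sample size). More than 50 specialists (Program adherence). About 20% of participants observed, at 1–2 sessions per specialist (Program adherence).

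**Input assumed.** The specialist ICC is not given. A range of 0.05 to 0.30 is used.

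**The article's own figures.** No figure is attached to the matrix, so there is none to reproduce. The observation plan is consistent with itself: 0.20 × 294 = 58.8, or about 59 participants, and 58.8/50 = 1.18 per specialist, which lies within 1–2. The average caseload is at most m = 294/50 = 5.88, since there are more than 50 specialists.

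**Step 1: precision by unit of analysis.** Near zero correlation, the 95% half-width on the Fisher z scale is 1.96/√(n − 3):

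- n = 294: 1.96/√291 = 0.115
- n = 59: 1.96/√56 = 0.26
- n = 50: 1.96/√47 = 0.29

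**Step 2: variance inflation with no true association.** The design effect for a correlation of clustered pairs is DE = 1 + (m − 1) × ICCx × ICCy. If one fidelity score is copied to a whole caseload, ICCx = 1. The true error of a nominal 5% two-sided test is then 2 × [1 − Φ(1.96/√DE)]. At ICC 0.10, for example, DE = 1 + 4.88 × 0.10 = 1.49, effective n = 294/1.49 = 198 and the error is 10.8%.

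**Step 3: simulation of naive Spearman tests.** Each scenario used 50 specialists, no true association and 4,000 runs, so the simulation standard error near 5% is √(0.05 × 0.95/4000), about 0.3 percentage points. Even caseloads were 5 or 6 participants. Uneven caseloads ran from 1 to 16. Both total 294. In the observed-only scenario, 41 specialists had one observed participant and 9 had two (59 in all).

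*Fidelity copied to the caseload (n = 294)*

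| ICC of other measure | DE | Effective n | Error, even | Error, uneven |
|---|---|---|---|---|
| 0.05 | 1.24 | 236 | 7.9% | 9.8% |
| 0.10 | 1.49 | 198 | 10.8% | 14.0% |
| 0.20 | 1.98 | 149 | 16.2% | 20.3% |
| 0.30 | 2.46 | 119 | 20.4% | 27.0% |

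*Two participant-level measures, same ICC for both (n = 294)*

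| ICC of both | DE | Error, even | Error, uneven |
|---|---|---|---|
| 0.05 | 1.01 | 4.9% | 5.0% |
| 0.10 | 1.05 | 5.0% | 5.6% |
| 0.20 | 1.20 | 6.8% | 8.5% |
| 0.30 | 1.44 | 9.3% | 13.2% |

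*Fidelity paired only with observed participants (n = 59).* Error was 5.1% to 6.1% across all ICCs tried, because almost no specialist contributes more than one pair.

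**The case against.** The strongest reply is that the article announces no test, p-value or confidence interval for the matrix. The 5% level under Sample size belongs to the falls comparison of the main trial. How an exploratory matrix handles clustering could be settled in an analysis plan that is not shown. This stands: a reader might infer that the plan's p-values and intervals are wrong, but the article commits to none. The point therefore concerns any inference that is later drawn from the matrix.

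A second reply is that the large error rates require a fidelity score to be copied to the whole caseload, and nothing in the article says that this will be done. Pairing each checklist with the participant who was observed is at least as natural, and it leaves the error close to nominal. This also stands. What remains is that the article attaches a sample of up to 294 to all four measures, while a row of observed pairs has about 59.

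A third is that clustering does not move a coefficient away from zero when there is no association; it only makes the coefficient more variable. That is correct, so it would be wrong to say that the matrix creates false relationships. When there is an association, however, a pooled coefficient for two participant-level measures blends differences between specialists with differences within a caseload.

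Finally, a reader might take Strengths and limitations to call specialist inconsistency the main limitation. It lists it as one of two, and sets common trainers, materials and ongoing support against it.

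**Conclusion.** The point holds in a limited form. The one named analysis of relationships joins a specialist-level score to participant-level scores without using the nesting that the article itself describes. Inference that treated the rows as independent could be materially too optimistic for the fidelity row: roughly 8–10%, 11–14% and 16–20% instead of 5% at ICCs of 0.05, 0.10 and 0.20 (even to uneven caseloads), if scores are copied to caseloads. There is practically no such harm if only observed participants are paired, although precision is then that of about 59 units. For participant-level pairs the harm is small unless both ICCs reach about 0.2.

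These sizes rest on assumed ICCs and on 50 specialists serving 294 participants. More specialists or fewer completers would reduce the average caseload and the inflation; uneven caseloads increase it. The analysis is exploratory and the remedy is cheap, so this is a modest improvement and not a serious flaw.

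**What to change.** Keep the rank correlations and make four changes.

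1. Compute the fidelity row at specialist level: each specialist's fidelity score against the mean dose, AFRIS and habit score of that specialist's participants (n about 50). The initial-session and later-session checklists have different ranges (39 to 117 and 29 to 87), so put the fidelity score on a common scale first, such as the mean item score.
2. State the unit of analysis and the number of units for every cell of the matrix.
3. Take any interval or p-value from a bootstrap that resamples specialists, or from a mixed model with a specialist random intercept.
4. Report the specialist ICC for dose, AFRIS and habit. These bear directly on the question, raised under Program adherence, of whether participants receive equivalent training.

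No new data are needed, because the CRM database already records the personnel involved in each session (Complete delivery). The cost is a few hours of analysis and somewhat wider intervals. For the fidelity row, the half-width near zero would be about 0.29, against the 0.115 that 294 independent pairs would suggest.

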## Methods

In this paper, we outline the aims and corresponding methods for the PlaTFORM process evaluation. The overarching aim is to understand the relationship between program implementation and acceptability, and program outcomes [11]. More specifically, (1) to explore if the PlaTFORM trial was delivered as intended (i.e. idelity and dose delivered) and (2) to understand whether, how and why the intervention had an impact, through exploring participants’ perspectives and enactment of the intervention (i.e. participant receipt and participant enactment).

We aim to recruit 588 community dwelling people with vision impairment, aged 50 years or above. After baseline assessment, participants will be randomly assigned to the intervention or control group. The intervention group will receive the v-LiFE program plus usual care (an Orientation and Mobility program), while the control group will receive only usual care. This process evaluation will only include data from the intervention group.

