### Program description

The v-LiFE program is designed to incorporate strength and balance activities into the everyday activities of older people with vision loss, living in the community, who are at high risk of falls. The intervention group will receive usual care as well the v-LiFE program over five weekly sessions, plus two booster visits and two phone calls within three months. If required, participants will receive up to two additional sessions. All sessions will be delivered in participants’ homes by O&M Specialists from Guide Dogs NSW/ACT. The control group will receive usual care.

The strength and balance activities will be catered to each participants’ physical function as they move through the program. As participants improve their strength and balance they will be encouraged to upgrade to more challenging exercises (i.e. reducing their base of support or increasing the weight lifted). O&M Specialists will be able to tailor their approach for each participant, which is in line with consensus that programs need to account for the individual context when delivering interventions [12]. Specially designed v-LiFE Participant manuals were produced for this population in audio, large print and electronic format.

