### Data analysis

Descriptive statistics will be used to summarise baseline demographic, vision and functional characteristics of intervention participants. In line with the MRC [10], quantitative data will be analysed prior to knowledge of trial outcomes to reduce bias. The quantitative and qualitative analyses will build upon one another, to help explain findings [10], and test the proposed logic model (Fig. 1).

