### Strengths and limitations

Over 50 O&M Specialists will deliver the v-LiFE program to participants, so there is the potential of inconsistencies along service delivery. However, O&M Specialists will receive two days of training in delivery of the v-LiFE program by the same trainers, and will receive the same training materials and ongoing support. The fidelity tool (program adherence) will capture how well the Specialists deliver the v-LiFE program to participants. The large number of Specialists delivering the program allows for a wider reach of the program and reflects real world conditions. Another limitation is that the participants themselves will predominantly be recruited from the Guide Dogs NSW/ACT database and may have already undergone O&M training. As a consequence, these participants may already be quite pro-active, compared to those who may not have accessed rehabilitation services in the past. Thus, participants may already be used to ongoing weekly O&M sessions and be more receptive to this program than someone who has not accessed services.

To our knowledge, this will be the first time a process evaluation will be embedded in a randomised controlled trail that looks at strength and balance and falls in older people with vision impairment. The process evaluation will be collecting both qualitative and quantitative data in a mixed-method design, allowing for a holistic understanding of participants engagement with the v-LiFE program.

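### The only stated analysis of relationships between process measures is a ranked correlation matrix in one arm with no stated adjustment, so baseline function and vision may distort it in either direction.

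*Protocol article*

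**What the plan says.** Under Quantitative data (within Data analysis), the article gives one method for relating the process measures to each other: "A correlation matrix (ranked) will determine any relationships between the process measures". No covariate, stratification or partial correlation is mentioned.

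The stated use of baseline data is descriptive: "Descriptive statistics will be used to summarise baseline demographic, vision and functional characteristics of intervention participants". The same section says that the quantitative and qualitative analyses will build on each other and test the logic model in Fig. 1.

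The Methods section limits the population: "This process evaluation will only include data from the intervention group".

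Two statements under Program description tie what is delivered to the participant's condition: "The strength and balance activities will be catered to each participants’ physical function as they move through the program", and "If required, participants will receive up to two additional sessions". Dose delivered is scored from 0 to 11.

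**The concern.** Dose delivered, the AFRIS score and the Self-Report Habit Index are all measured on the participant, within a single arm. Any entry characteristic that influences two of them produces a correlation between them, even where neither affects the other. Baseline physical function and vision are plausible candidates, and the dose score makes the route concrete because it counts sessions given on need.

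The article gives the matrix the task of determining relationships. Its Discussion says the findings will guide the continuing provision of fall prevention programs. A dose-habit correlation produced by baseline function could be taken as evidence that more contact builds habit. Where frailer participants receive the extra sessions and also form weaker habits, a real positive link could be hidden. The baseline data needed to examine this are already available.

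**Working it through.** **Inputs from the article**
- Data from up to 294 intervention participants (Sample size). With the 15% drop-out allowed for there, 294 × 0.85 = 249.9, or about 250.
- Dose delivered, 0 to 11: five weekly sessions, two booster visits, two calls and two extra sessions, 5 + 2 + 2 + 2 = 11. The top two points of the scale are therefore reached only through need-driven sessions.
- AFRIS, 6 to 42; habit index, 12 to 60.

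The article gives no effect size or power figure for the matrix, so there is no stated figure to reproduce first.

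**Assumption.** One baseline factor U correlates a with the first measure and b with the second, and the two measures have no direct link. The article gives no values for a and b, so a range is shown.

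**Expected raw correlation.** On the normal scale the induced Pearson correlation is a × b. The matching Spearman value is (6/π) × arcsin(ab/2):
- 0.2 and 0.2: ab = 0.04, Spearman 0.038
- 0.3 and 0.3: ab = 0.09, Spearman 0.086
- 0.4 and 0.4: ab = 0.16, Spearman 0.153
- −0.4 and 0.4: ab = −0.16, Spearman −0.153

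**Scale for comparison.** The smallest |r| with two-sided p < 0.05 is tanh(1.96 × √(1.06/(n − 3))). This is 0.118 at n = 294 and 0.128 at n = 250.

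**Simulation.** Several independent runs of 3,000 to 6,000 data sets per setting compared the raw Spearman correlation with the first-order partial Spearman correlation given U. Ranges show the spread across runs.

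| Loadings | Mean raw Spearman | Raw p < 0.05, n = 250 | Raw p < 0.05, n = 294 |
|---|---|---|---|
| 0.2 / 0.2 | 0.04 | 9% | 9–10% |
| 0.3 / 0.3 | 0.09 | 26–27% | 28–32% |
| 0.4 / 0.4 | 0.15 | 64–69% | 73–75% |
| −0.4 / 0.4 | −0.15 | 64–69% | 74–75% |

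The partial correlation averaged between −0.01 and 0.01, with p < 0.05 in about 4% to 6% of data sets, in every setting.

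**Dose as a bunched count.** Nine contacts are scheduled, so many scores may equal nine. If 80% of participants are assumed to sit at nine, the raw figures at n = 294 fall to about 0.07 (23%) for 0.3/0.3 and about 0.12 (54–55%) for 0.4/0.4. The distortion shrinks but remains.

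**Should elapsed time also be adjusted for?** Days from first session to the habit index are partly a consequence of dose, because added contacts can lengthen participation. Assume dose correlates 0.7 with elapsed time and habit builds only through time (0.3). The raw dose-habit Spearman is then (6/π) × arcsin(0.21/2) = 0.20, with p < 0.05 in about 94% of simulations at n = 294. After adjusting for time it is 0.01, with p < 0.05 in 5%. That adjustment would remove a real pathway, so it should not be made.

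**The case against.** The strongest reply is that silence is not error. The article never says that the correlations will be unadjusted, and the choice of covariates for exploratory associations is often left to an analysis plan. A Spearman coefficient is a correct description of a marginal association. This stands in part: nothing in the sentence is false. But the article does name a method and says what it will determine, so the point concerns a stated choice.

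The size is assumed. At loadings of 0.2 it is about 0.04. Even at 0.4 it is about 0.15, or 0.15² = 2.25% of shared rank variance. No significance threshold is planned, so the p < 0.05 shares only show how often a conventional reading would mislead. All of this stands.

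Three stronger readings are tempting, and the documents do not support them.
- A reader might infer that the matrix is itself the test of the logic model. The article assigns that test to the quantitative and qualitative analyses together, and Fig. 1 is not available to show whether it links dose to habit.
- A reader might infer that the bias must favour the logic model. Extra sessions given on need can push the dose-habit correlation downward as easily as up.
- A reader might take the remark under Strengths and limitations that "participants may already be used to ongoing weekly O&M sessions and be more receptive to this program" as an admission of confounding within the sample. It mainly concerns selection, comparing enrolled clients with people who have not used services. It does not say that prior clients receive more sessions. If most participants share that history, it varies little within the arm.

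**Conclusion.** The concern holds in a limited form. The sole stated quantitative analysis of relationships is pairwise, within one arm, with no adjustment stated and baseline vision and function put to descriptive use only. Under assumed loadings of 0.2 to 0.4 of equal sign, the spurious Spearman correlation is about 0.04 to 0.15. With opposite signs it is as large in the other direction, so a real link could be masked. Bunching of the dose score would reduce these values somewhat.

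The conclusion rests on baseline factors actually influencing at least two of the measures. The article makes this plausible but does not quantify it. The consequence is over- or under-interpretation of an exploratory process evaluation; the comparison of fall rates in the trial is untouched.

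**What to change.** Keep the raw matrix and describe its entries as marginal associations only. Beside it, for dose-AFRIS, dose-habit and AFRIS-habit, report partial Spearman correlations with 95% intervals. Adjust for a baseline physical function measure, a vision measure and age, with previous O&M service added where it is recorded. Name the covariates before the quantitative analysis, which the article already places ahead of knowledge of trial outcomes. Replace determine with explore. Do not adjust for days from first session to the habit index.

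The cost is a sentence or two in the plan and a few lines of code, using baseline data already available. Confounding by unmeasured factors will remain, and an adjusted correlation still does not establish a mechanism.

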**2.**	Complete Delivery (Dose delivered)	To what extent were all of the intended components of the v-LiFE program delivered to participants?	• O&M Specialists to record each time they complete a session, booster session, additional sessions and/or phone calls.	Quantitative	Higher scores indicate participants received a higher program dose	Self-monitoring of behaviour (Education/Incentivisation); Monitoring of behaviour by others without evidence of feedback (Coercion); Prompt/cues (Education)
**3.**	Participant Receipt (Dose received)	To what extent were participants engaged/satisfied with the v-LiFE program?	• Semi-structured interview (30 participants).	Qualitative	Analysis of transcripts using the BCW as a framework	Information about health consequences, self-monitoring of behaviour (Education); Monitoring of behaviour by others without evidence of feedback (Coercion)
			• Short answer survey (all participants).	Quantitative	Higher scores on the AFRIS indicate higher engagement to v-LiFE	
**4.**	Participant Enactment	To what extent were the participants completing the prescribed activities?	• The Self-Report Habit Index (post-program)	Quantitative	Higher scores on the Index indicate stronger habit formation	Self-monitoring of behaviour (Education/Incentivisation/Coercion); Feedback on behaviour (Education/Incentivisation/Coercion); Monitoring of outcome of behaviour by others without evidence of feedback (Incentivisation/Coercion

^a^ Michie et al. [13], BCW: Behaviour Change Wheel. AFRIS: Attitudes to Falls-Related Interventions Scale

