#### Complete delivery

Complete delivery (dose delivered) is a measure of the number of intended v-LiFE sessions and phone calls provided to participants [11]. In order for complete delivery, O&M Specialists will be required to deliver 5 weekly sessions, 2 booster visits and 2 follow-up phone calls. O&M Specialists are also able to provide an additional 2 sessions if required by the participants. Program session data will be collected from the Guide Dogs Customer Relationship Manager (CRM) database. As with any O&M program and associated program sessions, O&M Specialists will be required to detail the name, date, travel time, travel distance, session objectives and session outcomes in Guide Dogs CRM database. This will be a record of sessions and phone calls and personnel involved.

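### The 0–11 score for complete delivery counts two optional sessions alongside the nine intended contacts, so totals of 9 and 10 do not show whether the intended programme was delivered

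*Protocol article*

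**What the plan says.** Three places in the protocol article bear on this measure.

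- **Definition (Complete delivery).** "Complete delivery (dose delivered) is a measure of the number of intended v-LiFE sessions and phone calls provided to participants". For this, "O&M Specialists will be required to deliver 5 weekly sessions, 2 booster visits and 2 follow-up phone calls". The section then adds that "O&M Specialists are also able to provide an additional 2 sessions if required by the participants". The Program description agrees that these sessions are conditional: "If required, participants will receive up to two additional sessions".
- **Question and reading (Table 1, row 2).** The question is "To what extent were all of the intended components of the v-LiFE program delivered to participants". The score is to be read as follows: "Higher scores indicate participants received a higher program dose". For recording, the row asks "O&M Specialists to record each time they complete a session, booster session, additional sessions and/or phone calls".
- **Analysed variable (Quantitative data).** The measure is the "number of v-LiFE sessions and phone calls delivered to participants by O&M Specialists, as a continuous variable (range 0 to 11". The same section plans descriptive summaries of the process measures and a ranked correlation matrix between them.

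**The concern.** The definition and the Table 1 question concern contacts that were intended for everyone. The analysed variable is a total that also includes contacts given only to some participants, on need. Two things follow.

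First, an additional session can stand in for a missed weekly session, booster visit or call without leaving a trace in the score. The first specific aim, in Methods, is to establish whether the trial was delivered as intended, and dose delivered is one of the two measures named for it. A score that can hide a missed component serves that aim poorly.

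Second, the top two values of the scale are open only to participants who had extra sessions. Someone who received exactly the planned programme ranks below them. The correlation matrix uses ranks, so it takes this ordering at face value. If the reasons for giving extra sessions are related to habit strength or to attitude to the programme, the correlations of dose with those measures mix amount delivered with need.

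**Working it through.** **Inputs** (Complete delivery section; Program description):

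- Weekly sessions W: 0–5
- Booster visits B: 0–2
- Phone calls C: 0–2
- Additional sessions A: 0–2

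**Step 1. Reproduce the stated range.** Intended contacts: 5 + 2 + 2 = 9. With additional sessions: 9 + 2 = 11. This matches the article's upper limit, so the additional sessions must be in the score. The two calls are already among the nine; adding them again would give 9 + 2 + 2 = 13, which the article does not state.

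**Step 2. List every pattern (W, B, C, A) by total T = W + B + C + A.** Delivery is complete only when (W, B, C) = (5, 2, 2).

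| Total T | Patterns | Complete | Incomplete | Intended contacts | Fewest additional sessions |
|---|---|---|---|---|---|
| 8 | 17 | 0 | 17 | 6–8 | 0 |
| 9 | 10 | 1 | 9 | 7–9 | 0 |
| 10 | 4 | 1 | 3 | 8–9 | 1 |
| 11 | 1 | 1 | 0 | 9 | 2 |

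Totals of 0–7 likewise contain no complete pattern.

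**Step 3. Patterns at 9 and 10.**

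- T = 9, complete: (5,2,2,0).
- T = 9, one intended contact missing: (4,2,2,1), (5,1,2,1), (5,2,1,1).
- T = 9, two intended contacts missing: (3,2,2,2), (4,1,2,2), (4,2,1,2), (5,0,2,2), (5,1,1,2), (5,2,0,2).
- T = 10, complete: (5,2,2,1).
- T = 10, one intended contact missing: (4,2,2,2), (5,1,2,2), (5,2,1,2).

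So 9 + 3 = 12 incomplete patterns score at or above the 9 earned by exact delivery of the planned programme. In (5,0,2,2) both booster visits are absent, and in (5,2,0,2) both calls are absent; each still scores 9.

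**Step 4. Is there a usable cut-off?** T ≥ 9 captures every complete case but admits the 12 incomplete patterns. T ≥ 10 drops the participant with exact delivery and still admits 3 incomplete patterns. T = 11 is never wrong, but counts as complete only those who also had both additional sessions. No threshold on the total separates complete from incomplete delivery.

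**Step 5. Effect on ranks.** (5,2,2,0) scores 9 and (4,2,2,2) scores 10. The participant with all nine intended contacts ranks below one who missed a weekly session and had two extra sessions.

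These are counts of possible patterns, not probabilities. The article gives no expected frequency of additional sessions or of missed contacts.

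**The case against.** The best defence is that 0–11 is a sensible count of total contact. The section on the intervention delivery component lists the additional sessions as one of the ways the programme is delivered, and Table 1 reads the score simply as dose. On that view the variable suits the label dose delivered and only the label complete delivery is loose. This stands in part: the total is a legitimate description of contact. It does not answer the question in the same table row, which is about intended components.

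It can also be said that each type of contact is to be recorded, so an intended-only score can be derived later, and that a condensed article may leave a breakdown to a fuller plan. The first point is right and makes the fix cheap. The second does not excuse the variable, because the article itself states it and its range.

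A reader might infer more than the documents support:

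- That the phone calls are optional extras. They are among the nine.
- That the score can never show whether delivery was complete. It can at 0–8 and at 11.
- That high scorers were struggling, or that the correlations are flattened or reversed. The article says only that extra sessions are given if required. It gives no criteria, no frequency and no link to the other measures, so neither the size nor the direction of any confounding is established.

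**Conclusion.** The point holds. The analysed variable does not match the construct that the article defines. Totals of 9 and 10, which lie at the boundary for complete delivery, do not show whether the intended programme was delivered: 9 of 10 and 3 of 4 patterns respectively are incomplete. Totals of 10–11 occur only with additional sessions, so ranked correlations with dose may be confounded by need to an extent that cannot be quantified from the article.

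This rests on two readings: that the step from 9 to 11 is the two additional sessions, which is the only combination of the listed contacts that gives the stated range; and that each contact counts as one, as a simple count implies. How many participants would be misread depends on how often extra sessions are given to people who missed intended contacts, and this is unknown.

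The severity is moderate. The problem affects one of four process measures, used for description and correlation. It does not touch the main trial's falls outcome or its sample size.

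**What to change.** In Quantitative data, and correspondingly in Table 1:

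1. Define dose delivered as the number of intended contacts completed, range 0–9.
2. Report its components (weekly 0–5, booster 0–2, calls 0–2) and complete delivery as yes/no, where yes means 9 of 9.
3. Report additional sessions (0–2) as a separate variable.
4. Use the 0–9 score as the main dose measure in the correlation matrix. The 0–11 total may be kept as a secondary description of overall contact.
5. State how a session is classed as additional when the data are extracted from the service provider's database. Table 1 has the contact types recorded, but the list of database fields under Complete delivery does not name contact type.

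The cost is analysis wording and a coding rule. No new data should be needed, provided that the records distinguish the contact types as Table 1 indicates, and nothing about the intervention changes. Because the article plans to analyse the quantitative process data before trial outcomes are known, the definition should be settled before that analysis starts.
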